Fluoxetine is a relatively cheap, widely available and generally well-tolerated medication with a good safety profile, and is widely prescribed in people with epilepsy [38], owing to the high comorbidity of depression and epilepsy [39]. Whilst the British National Formulary (BNF) urges caution for the prescription of fluoxetine in this population based on experimental increased seizure risk [40], most studies suggest the anti-depressants do not worsen seizures and may have a protective, anti-convulsant effect at therapeutic doses [41–46]. Further, there is evidence to suggest that fluoxetine can increase suicidal thoughts and suicidal ideation in adolescents [47–49], but this is only in people being treated for active ongoing depression. Whilst these factors pose a potential risk, it is possible to mitigate these risks, and thus, fluoxetine treatment in the context of remedying an unmet therapeutic need in people with TLE warrants further investigation.

Learning and memory in people with TLE can be measured using a number of hippocampal-dependent measures of learning. This includes the virtual water maze (a direct correlate of the widely used rodent version and described in [17]), pattern separation tasks and SenseCam paradigm. Pattern separation tasks serve as a highly hippocampal-dependent test of location memory that can be automated in both rodent [50] and human [51] models of testing. There is evidence to suggest that discrimination of pattern separation, especially when finely spaced, is dependent on neurogenesis [52]. The SenseCam paradigm allows the testing of learning and memory in a real-world setting which may be more applicable to situations of daily living where memory deficits may be more problematic. This has previously been used to demonstrate accelerated forgetting in people with transient epileptic amnesia [53].

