### Screening assessments

Potentially eligible participants will be invited to attend a screening assessment. This will include a medical history, blood tests for liver enzymes and electrolytes, completion of the HADS, completion of the WASI and a structural 3T MRI to confirm laterality of HS (see Table 1). Any participant who declares a history or family history of heart conditions predisposing to arrhythmia will also receive an electrocardiogram (ECG). Participants who are found to have any of the following, bi-lateral HS, an intelligence quotient (IQ) of 74 or below, a HADS score of 12 or more, an aspartate transferase level more than 2.5 times the upper limit of normal, hypokalemia, hypomagnesia or an abnormal ECG (Q-T interval prolongation, ventricular arrhythmia or Torsades de pointes), will be excluded from the trial. As the HADS is a guideline rather than absolute measure of anxiety or depression, participants who score 11 (borderline) will undergo review by a consultant psychiatrist. If the psychiatrist does not think that the participant has active ongoing anxiety or depression, they will be able to continue in the trial.

**Table 1 Tab1:** Schedule of trial assessments

Procedure	Schedule											
	Eligibility assessment	Baseline assessments			Study drug	Follow-up assessment 1				Follow up assessment 2		
Visit number	1	2	3	4		5	6	7	8	9	10	11
Time-point of visit	T-1 to 4 weeks	T0	T1	T-21	T22-T104	T83	T84	T[97-104]	T104	T164	T165	T185
Written informed consent	X											
HADS	X											
WASI	X											
Blood tests (liver function, electrolytes)	X											
ECG (where indicated)	X											
MRI Safety Questionnaire	X							X				
Issue of seizure diary	X											
Structural MRI	X							X				
Review of seizure frequency		X	X	X		X	X		X	X	X	X
QOLIE-31		X				X				X		
Written Cognitive Assessments		X										
Virtual Water Maze Task		X	X	X		X	X		X	X	X	X
Pattern separation task		X				X				X		
Word Lists		X	X	X		X	X		X	X	X	X
Medical Outcomes Sleep Survey		X				X				X		
Issue of SenseCam		X				X				X		
Testing of SenseCam		X	X	X		X	X		X	X	X	X

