A 3T MRI will be performed at the screening assessment and will be repeated following trial treatment. The scanning protocol will include structural sequences required to confirm unilateral sclerosis (FLAIR as well as T1- and T2-weighted images), as well as a multi-shell diffusion-weighted sequence with which we will be able to derive voxel-wise maps of water diffusion indices. These will include diffusion tensor MRI (DT-MRI) measures such as fractional anisotropy (FA) and mean diffusivity (MD), which are sensitive to grey and white matter microstructural abnormalities in a variety of neurological conditions including temporal lobe epilepsy [66–68]. These measures can be extracted from specific regions-of-interest (ROIs) and compared pre- versus post-treatment to test whether fluoxetine treatment affects grey and/or white matter tissue microstructure (e.g., in the hippocampus and its associated white matter pathways). With these measures, we can also examine whether performance in the cognitive tasks is associated with DT-MRI measures in the same ROIs. Prior to receiving an MRI, participants will be required to complete a questionnaire to ensure that it is safe for them to have the scan.

All participants will be provided with seizure diaries at the start of the baseline assessments. They will be asked to record any seizures in the diary until they complete the final follow-up assessment. This diary will be reviewed at each follow-up and testing session to ensure that seizure frequency has not increased significantly.

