### Trial treatment

Following randomisation, participants will be allocated to receive either 20 mg fluoxetine per day or matched placebo. Fluoxetine will be obtained from Bristol Laboratories and over encapsulated at St. Mary’s Pharmaceutical Unit, Cardiff. Placebo to match will be manufactured in identical capsules using maize-based cellulose as the capsule filler. The fluoxetine or placebo capsules are taken orally once daily for a total of 81 days; 60 days of treatment followed by a further 21 days whilst the first follow-up assessments are conducted to prevent confounding effects of washout at the 21-day test point owing to the short half-life of fluoxetine [69]. Participants will be asked to bring trial medication with them to each study visit where study researchers will perform pill counts for assessing adherence. Adherence will be measured by recording the number of pills returned and using this in conjunction with the number of doses supplied to calculate a percentage of the number of doses that should have been taken in the observed period. Although we will specifically be excluding participants with active depression, due to the risk of fluoxetine treatment increasing suicidal thoughts and suicidal ideation in adolescents [47–49], we will perform remote checks on the mental health on participants. This will be done via a telephone call with an experienced specialist epilepsy nurse 2 to 3 weeks after commencing treatment, when the risk is at its highest. Any participant indicating thoughts of suicide or depressive behaviour will be referred to the trial psychiatrist for immediate follow-up.

The dose chosen for the trial was on the basis of an equivalent dose being efficacious in animal models [31] and because it is below the limit at which tapering is required for medication withdrawal [70, 71], so participants will not receive tapered doses at the end of the treatment period or if cessation of trial treatment is required. If a participant who has stopped the trial treatment experiences any symptoms of withdrawal, they will be unblinded so that if they received fluoxetine, treatment can be resumed and gradually reduced over 1–2 weeks.

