### Safety

Participants will be monitored for adverse events (AE) for the duration of the trial. Researchers will prompt participants to recount any adverse events experienced at each follow-up visit. Participants will also be encouraged to contact the team directly in between follow-up visits to report any incidence of AE to the trial team by the use of a trial-specific phone number monitored 24 h a day. Any AE that meets the criteria for a serious event will be reported immediately, and causality and expectedness will be assessed according to the Summary of Product Characteristics. We will forward standard timelines and procedures for the reporting of serious events to regulatory authorities.

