The findings of this trial will advance current knowledge in terms of understanding how fluoxetine is tolerated in people with epilepsy. The effect of fluoxetine on seizure frequency is still debated [35–39], so the tracking of seizure frequency in participants of this trial will provide further information for epilepsy clinicians concerned about prescribing fluoxetine to their patients.

A particular strength of this study will be realised through obtaining the views and opinions of participants taking part and perhaps, more importantly, those who chose not to take part in the trial will contribute to the understanding of potential barriers of facilitators underpinning the participation of people with epilepsy in this trial. Further, this information may also contribute to the understanding of why people with epilepsy may or may not take part in research and clinical trials in general, providing valuable information for the future development of research studies involving people with epilepsy.

Participants receiving the intervention in this trial have the potential to benefit from improved learning and memory using a relatively, cheap, widely available and generally well-tolerated medication, which may improve quality of life in people with TLE [8]. This could also have further societal benefits by reducing demand on carers and further enabling people with TLE to have active and productive working lives.

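### No seizure-diary review is scheduled in the first 60 or so days on drug; the nurse call already planned at 2–3 weeks could include one

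*Protocol article*

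**What the plan says.** The Trial assessments section has participants record seizures in a diary up to the final follow-up assessment, and says of it: "This diary will be reviewed at each follow-up and testing session to ensure that seizure frequency has not increased significantly". Table 1 (under Screening assessments) has a row "Review of seizure frequency" marked at visits 2 to 6 and 8 to 11. The study-drug column, T22 to T104, is blank in that row.

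The Backgrounds section names two risks of fluoxetine, seizures and suicidal ideation. On seizures it notes that the British National Formulary "urges caution for the prescription of fluoxetine in this population based on experimental increased seizure risk", and adds that most studies suggest no worsening and perhaps a protective effect. Of both risks it says: "Whilst these factors pose a potential risk, it is possible to mitigate these risks". The Discussion says: "The effect of fluoxetine on seizure frequency is still debated".

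For suicidal ideation, the Trial treatment section plans active contact on drug: "we will perform remote checks on the mental health on participants", and "This will be done via a telephone call with an experienced specialist epilepsy nurse 2 to 3 weeks after commencing treatment". For events between visits, the Safety section relies on the participant: "Participants will also be encouraged to contact the team directly in between follow-up visits to report any incidence of AE", using a telephone line staffed around the clock. Researchers' own prompts for adverse events are tied to follow-up visits.

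**The concern.** The review times follow the cognitive testing days (days 1, 2 and 21 of each block), not exposure to the drug. Reviews fall one day apart at T83 and T84, yet there is none in the first 60 or so days of a newly started drug. A check meant to ensure that seizures have not increased cannot serve that purpose while none is scheduled.

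The article also treats its two named risks differently. For suicidal ideation it makes an active call early on drug, even though it excludes active depression. For seizures, in a trial where every participant has epilepsy, it describes only reporting started by the participant over the same interval. These participants are being studied for memory impairment, and the Backgrounds section notes that complex partial seizures alter consciousness, so self-report is not a dependable substitute for a prompted check.

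What is at stake is safety monitoring: how late an unreported increase on treatment could be found. The analysis of seizure frequency is not at issue.

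**Working it through.** The protocol states no figure on this point to reproduce. The check is day arithmetic on its schedule.

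**Inputs**
- Reviews marked in Table 1: T0, T1, T21, T83, T84, T104, T164, T165, T185. The third is printed as T-21 and is read here as T21, the last baseline visit.
- Study drug by Table 1: T22 to T104.
- Study drug by Trial treatment: 81 days, made up of 60 days and then 21 days during follow-up assessment 1.
- Nurse call by Trial treatment: 2 to 3 weeks (14 to 21 days) after drug start.

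**Gaps between successive reviews (days)**
1, 20, **62** (T21 to T83), 1, 20, 60 (T104 to T164, off drug), 1, 20.

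**Drug time before the first on-drug review**
- Table 1: T22 to T82 inclusive = 82 − 22 + 1 = 61 days. The whole drug period is 104 − 22 + 1 = 83 days. 61/83 = 73%.
- Trial treatment: 60/81 = 74%.

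The three on-drug reviews (T83, T84, T104) all fall in the last 83 − 61 = 22 days.

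**With a diary check at the nurse call**
- Call date: T22 + 14 = T36 to T22 + 21 = T43.
- First on-drug check: 14 to 21 days after drug start instead of 61.
- Remaining interval to T83: 83 − 36 = 47 days, or 83 − 43 = 40 days. Each exceeds the interval before the call, so it is the longest unreviewed on-drug stretch.
- Reduction: (61 − 47)/61 = 23% to (61 − 40)/61 = 34%.

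**The case against.** The strongest reply is that nothing here is contradictory. The text promises review at follow-up and testing sessions, and Table 1 marks all nine of them. That is correct, so the point is a weak scheduling choice and not an inconsistency.

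Second, the article condenses a full protocol (version 8.0), which may give the nurse call wider content than the article reports. This stands as a limit: the article describes only the call's mental-health purpose and does not say that nothing else is asked. The review times, however, are fixed in the article's own text and table, so the published schedule has the gap either way.

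Third, the seizure risk may be small, and the call is timed for the peak of a different risk. Both are fair. Nothing in the article says seizure risk peaks at 2 to 3 weeks; the timing is proposed because the contact already exists.

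Fourth, other safeguards apply: the 24-hour line, exclusion of poorly controlled seizures, status epilepticus as a ground for unblinding, routine central monitoring with monthly oversight, and the data monitoring committee. They reduce the risk but do not replace an active check. The line depends on the participant, the exclusion as worded applies to people undergoing active anti-epileptic drug changes, and the monitoring bodies see only what has been collected.

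Finally, a check without a threshold will raise chance alerts. Assuming Poisson counts, an unchanged rate and two equal 21-day windows, about 35% of participants would show some increase at a mean of 1 seizure per window, and about 43% at a mean of 4. This is true, but with about 20 participants and a clinician judging each report, the burden is small. The day counts above describe the schedule only; no missed-event rate can be derived from the article.

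**Conclusion.** The concern holds, as a minor point about safety monitoring. By the published schedule, the first seizure review on drug comes after 61 of 83 drug days (73%), or 60 of 81 (74%) by the stated treatment length. Until then, detecting an increase relies on the participant reporting it. Using the nurse call would bring the first check forward to 14–21 days and cut the longest unreviewed on-drug interval to 40–47 days.

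This rests on reading T-21 as T21, on the Table 1 drug start of T22, and on the article's description of the call as a mental-health check. Existing safeguards limit the risk, so the gain is modest. Confidence is medium, because the full protocol may already extend the call.

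**What to change.** Extend the existing call by the specialist epilepsy nurse to include a seizure-diary check and an adverse-event prompt, for all participants in both arms, and show the call in Table 1. Pass any reported increase to the chief investigator or clinically qualified delegate, roles already named in the randomisation and blinding section, for clinical judgement. If the full protocol's call already does this, only the article's description and Table 1 need changing.

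The cost is a few minutes on each existing call and one case report form page for about 20 participants, with no new visit or staff. Because the trial is already recruiting, the change would have to be introduced during its conduct, and participants past that stage would not have had the check. Randomisation, blinding and sample size are unaffected. The change does not close the gap: 40–47 on-drug days would still pass without a scheduled review.

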### Randomisation, allocation concealment and blinding

Eligible participants will be randomised in a 1: 1 ratio (fluoxetine to placebo) using random permuted blocks, stratified by status of laterality of HS (left versus right) following baseline assessments. Each block of allocations will be equally balanced between active and placebo. A computer-generated sequence will select which permutation to use for every block of participants. Block size and permutations will remain concealed to the trial team. The trial treatment will be dispensed by the local clinical trial pharmacy according to the pre-specified list provided by the trial statisticians. Identical capsules containing either fluoxetine or placebo will be packaged in identical high-density polyethlyene containers with tamper evident closure. Each package will be labelled in compliance with Annex 13 and according to EU mandated Good Manufacturing Practice. A detachable tear off section will allow maintenance of blinding at the point of dispensation. Details of allocation will be kept within the participant accountability records within pharmacy and will not be revealed to the trial team unless emergency unblinding is required. Unblinding will be permitted if the participant (1) withdraws due to a significant decrease in mood, (2) exhibits an episode of status epilepticus, (3) experiences severe withdrawal symptoms and (4) requires the prescription of any medication that should not be taken in conjunction with fluoxetine as detailed in prescribing guidelines. If any of these criteria are met, the information will be passed to the chief investigator (CI) or clinically qualified delegate who will confirm the need for unblinding. The CI or trial manager will contact the dispensing pharmacy to review the accountability records for that participant. In emergency situations, the CI or clinically qualified delegate will contact the on-call pharmacist to review the relevant participant accountability log.

### Trial treatment

Following randomisation, participants will be allocated to receive either 20 mg fluoxetine per day or matched placebo. Fluoxetine will be obtained from Bristol Laboratories and over encapsulated at St. Mary’s Pharmaceutical Unit, Cardiff. Placebo to match will be manufactured in identical capsules using maize-based cellulose as the capsule filler. The fluoxetine or placebo capsules are taken orally once daily for a total of 81 days; 60 days of treatment followed by a further 21 days whilst the first follow-up assessments are conducted to prevent confounding effects of washout at the 21-day test point owing to the short half-life of fluoxetine [69]. Participants will be asked to bring trial medication with them to each study visit where study researchers will perform pill counts for assessing adherence. Adherence will be measured by recording the number of pills returned and using this in conjunction with the number of doses supplied to calculate a percentage of the number of doses that should have been taken in the observed period. Although we will specifically be excluding participants with active depression, due to the risk of fluoxetine treatment increasing suicidal thoughts and suicidal ideation in adolescents [47–49], we will perform remote checks on the mental health on participants. This will be done via a telephone call with an experienced specialist epilepsy nurse 2 to 3 weeks after commencing treatment, when the risk is at its highest. Any participant indicating thoughts of suicide or depressive behaviour will be referred to the trial psychiatrist for immediate follow-up.

The dose chosen for the trial was on the basis of an equivalent dose being efficacious in animal models [31] and because it is below the limit at which tapering is required for medication withdrawal [70, 71], so participants will not receive tapered doses at the end of the treatment period or if cessation of trial treatment is required. If a participant who has stopped the trial treatment experiences any symptoms of withdrawal, they will be unblinded so that if they received fluoxetine, treatment can be resumed and gradually reduced over 1–2 weeks.

Participants will not be able to take any of the medicines listed in the exclusion criteria for the duration of the trial, but they will be permitted to continue with their current AED regime. Participants currently on carbamazepine therapy will be cautioned to self-monitor for exacerbation of drug side effects.

### Safety

Participants will be monitored for adverse events (AE) for the duration of the trial. Researchers will prompt participants to recount any adverse events experienced at each follow-up visit. Participants will also be encouraged to contact the team directly in between follow-up visits to report any incidence of AE to the trial team by the use of a trial-specific phone number monitored 24 h a day. Any AE that meets the criteria for a serious event will be reported immediately, and causality and expectedness will be assessed according to the Summary of Product Characteristics. We will forward standard timelines and procedures for the reporting of serious events to regulatory authorities.

### Feasibility outcomes

The primary outcome of this trial is feasibility which will be assessed by looking at measures of recruitment (number of participants recruited, percentage of people approached willing to participate and percentage of participants to pass screening), retention (percentage of participants still on study medication at follow-up assessment one and percentage of partially active participants at follow-up assessment one) and adherence (to study medication) according to pre-specified criteria, the detail of which can be found in Table 2. Each criterion is stratified into green (feasibility clearly demonstrated), amber (feasibility possibly demonstrated but requires further consideration) and red (feasibility not demonstrated). All criteria would need to be determined to be green or amber to progress to a full efficacy trial without major re-design of the study.

**Table 2 Tab2:** Progression criteria for assessing feasibility of trial design

Variable		Progression criteria		
		Red	Amber	Green
Recruitment	Percentage of participants approached willing to participate	< 5%	5–20%	> 20%
	Percentage of participants screened actually recruited	< 50%	50–75%	> 75%
	Number of participants recruited	< 8	8–16	> 16
	Number of participants recruited within timeframe (1 year)	< 2	2–15	> 15
Retention	Percentage of participants still on study medication at follow-up assessment 1	< 30%	30–60%	> 60%
	Percentage of partially active* trial participants at follow-up assessment 1	< 50%	50–80%	> 80%
	Percentage of partially active trial participants at follow-up assessment 2	Not subject to progression criteria		
Adherence	Pill count (compliance) over 81 days	< 50%	50–80%	> 80%

*This would include participants that have partially withdrawn from the study, for example, stopping study medication but continuing with follow-up assessments

